### Sample Size Calculation

The minimum required sample size is calculated using the single-population proportion formula [31], based on T2DM with MetS prevalence of approximately 11.2% in Hong Kong [32]. With a 95% confidence level, a precision of SD 3%, and an assumed nonresponse rate of 10%, the study aims to recruit 470 participants.

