### Statistical Analysis

Statistical analysis will be performed using SPSS (version 29.0; IBM Corp), Python (version 3.13.9), and R (version 4.5.2; R Foundation for Statistical Computing) software. Missing values will be imputed by multiple imputation using the chained equation method. Quantitative data will be summarized as mean (SD) if normally distributed or as median and interquartile range otherwise. Latent class analysis will be used to identify the TCM syndrome patterns. Factor analysis will be used to reduce the dimensions of TCM syndrome elements and explore their underlying structure. Data suitability will be evaluated using the Kaiser-Meyer-Olkin measure and Bartlett's test of sphericity. Principal component analysis with varimax rotation will be employed to extract the common factors. Based on the factor analysis results, hierarchical cluster analysis will be performed to classify TCM syndrome elements. Cluster boundaries will be determined by identifying large distances between successive fusion levels in the dendrogram. The adjusted Rand index will be used for measuring the agreement between classifications.

For the comparison of quantitative data, one-way analysis of variance will be used if the assumptions of normality and homogeneity of variance are met. Otherwise, the Kruskal-Wallis test will be used. Categorical data will be expressed as numbers and percentages, and comparisons will be conducted using the chi-square test or Fisher exact test, as appropriate. Spearman correlation analysis will be employed to evaluate correlations between continuous variables, and Kendall’s tau-b analysis will be used for ordinal variables. Logistic regression will be performed to examine the relationship between syndrome differentiation and MetS components. A 2-sided value of *P*<.05 will be considered statistically significant.

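### The Kruskal-Wallis fallback does not remedy unequal variances: for normally distributed variables it can miss the 5% level when group sizes and SDs both differ; use Welch's ANOVA

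*Protocol article*

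**What the plan says.** The Statistical Analysis section of the protocol article fixes a two-branch rule for quantitative variables: one-way ANOVA if "the assumptions of normality and homogeneity of variance are met. Otherwise, the Kruskal-Wallis test will be used". ANOVA thus needs both conditions, and failure of either one leads to Kruskal-Wallis. No unequal-variance method is named.

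The same section chooses the summary statistic on normality alone: mean (SD) for normally distributed variables, median and interquartile range for the rest. The level is fixed as well: "A 2-sided value of *P*<.05 will be considered statistically significant".

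The section does not name the groups to be compared. The natural reading is the syndrome groups, since the aims relate syndromes to metabolic measures, lifestyle and quality of life. Those groups come from the data: "Latent class analysis will be used to identify the TCM syndrome patterns". Their number, sizes and within-group SDs are not given. The Sample Size Calculation section states only the total: "the study aims to recruit 470 participants".

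**The concern.** Kruskal-Wallis holds its level when the group distributions are identical under the null hypothesis. Unequal spread breaks that condition, so the fallback does not cure the fault that triggers it.

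The gap lies with variables that are normal but unequal in variance. They are summarised by means, so readers will take a significant result as a difference in means, yet the test does not hold 5% for that hypothesis. Nothing makes latent classes equal in size, and groups expected to differ metabolically may also differ in spread.

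At stake is the reading of secondary comparisons of syndromes on measures such as glucose, blood pressure, sleep score and quality of life. If small classes are the more variable ones, false positives become more frequent. If large classes are, the test becomes conservative.

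This concerns a choice that the article states, not detail left to an analysis plan.

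**Working it through.** **The plan's own figure.** The article gives no error rate for the rule. Its one computed figure is the sample size, which supplies N. With prevalence 11.2% ("based on T2DM with MetS prevalence of approximately 11.2% in Hong Kong"), 95% confidence, precision 3% and nonresponse 10%:

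n = 1.96² × 0.112 × 0.888 / 0.03² = 424.5, rounded up to 425.

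425 / 0.90 = 472.2, rounded up to 473; or 425 × 1.10 = 467.5, rounded up to 468. Both are close to the stated 470, so 470 was used below.

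**Why Kruskal-Wallis fails here.** The statistic is H = 12 / [N(N+1)] × Σ nᵢ (R̄ᵢ − (N+1)/2)², referred to chi-square with k − 1 degrees of freedom. The constant 12 / [N(N+1)] comes from the variance of ranks when all N observations are exchangeable. If spreads differ, the mean ranks do not have that variance even when all means and medians are equal. Welch's ANOVA instead weights each group by wᵢ = nᵢ / sᵢ², its own variance estimate.

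**Inputs from the article.** N = 470; two-sided 0.05; ANOVA if both checks pass, otherwise Kruskal-Wallis.

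**Inputs assumed, because the article gives none.**
- Normal data with equal means.
- Group sizes 94 × 5; 188/118/82/47/35; or 280/120/70.
- SDs evenly spaced from 1 to the stated ratio and ordered with group size.
- Checks: Shapiro-Wilk in each group and median-centred Levene, each at 0.05.
- 3,000 runs per scenario, so the Monte Carlo standard error near 5% is √(0.05 × 0.95 / 3000) = 0.4 percentage points.

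**Rejection rate of the stated rule under equal means:**

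| Groups | Most variable | SD ratio 1.25 | 1.5 | 2 | 3 |
|---|---|---|---|---|---|
| 5 equal | one of five equal groups | 4.8% | 5.5% | 5.6% | 5.2% |
| 5 unequal | smallest | 7.1% | 8.4% | 9.0% | 12.0% |
| 5 unequal | largest | 3.4% | 2.7% | 2.3% | 2.7% |
| 3 unequal | smallest | 7.1% | 7.9% | 10.1% | 12.8% |
| 3 unequal | largest | 3.7% | 3.6% | 1.9% | 1.7% |

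With equal SDs the rule gave 4.7-4.9%. Welch's ANOVA gave 4.1-5.8% over all these scenarios.

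**Which branch is responsible.** Levene's test rejected in 29-54% of runs at ratio 1.25, in 80-98% at 1.5 and in at least 99.8% at 2 or more. At ratio 1.25 both branches contribute. In the five unequal groups with the smallest most variable, ANOVA alone gave 7.5% and Kruskal-Wallis alone 6.6%. From ratio 2 upward the result is almost wholly that of Kruskal-Wallis. Plain ANOVA in the worst cases reached 20-22%, so the switch reduces the distortion without removing it.

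**Ordering of the SDs.** With sizes 180/120/90/60 or 220/120/70/40 and SDs 1, 1.25, 1.5 and 2 assigned so as not to follow group size, Kruskal-Wallis rejected in 3.9-6.4% and 3.8-7.6% of runs (4,000 each). The clear departures need alignment between size and spread.

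**The case against.** The strongest reply is that the distortion is conditional. It needs group sizes and SDs that both differ and that line up. With equal sizes the rule is sound even at an SD ratio of 3, and with unordered SDs it is mostly close to 5%. The article gives no class sizes or SDs, so neither the size nor the direction of an error can be established from it. This stands and limits the point.

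A second reply is that if the null hypothesis is identical distributions, a rejection caused by unequal spread is no false positive. The article does not say which null it means. For normal variables, however, it reports means, so that defence does not match how the result will be read.

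A third reply is that the primary outcome is syndrome differentiation itself, so these comparisons are secondary. The article also acknowledges the causal limits of its cross-sectional design. This stands too, and it keeps the point small.

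A reader might go further and infer that the skewed variables are worst affected. Simulated skewed data (five unequal groups, smallest most variable, SD ratios 1.5 and 2, 2,000 runs each) did give 15.5% and 30.4% under equal means. But there the medians differ, and the article summarises such variables by medians. Under equal medians the rates were 8.8% and 10.2%. Those variables also reach Kruskal-Wallis through non-normality, where the test is a conventional choice. The larger figures therefore do not measure a fault in the plan.

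**Conclusion.** The point holds in a limited form. The stated rule sends normal variables with unequal variances to a test that does not protect the 5% level for a difference in means. Under the assumed unequal group sizes and SD ratios of 1.25-3, aligned with size, the rate is about 7-13% if the smaller groups are more variable and about 2-4% if the larger groups are. With equal sizes it is about 5-6%.

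A reader might infer that the syndrome comparisons in general run well away from 5%. The article does not support that: it gives no class sizes or SDs, and several plausible configurations leave the level nearly intact. What can be said is that the fallback gives no assurance of the level, while Welch's ANOVA stayed at about 4-6% in every normal-data scenario. This is a worthwhile small correction to secondary analyses. It does not touch the primary outcome or the sample size.

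**What to change.** For approximately normal variables, use Welch's ANOVA, or a linear model with heteroscedasticity-robust standard errors, whether or not variances look equal. Drop the variance pre-test. Report group means with 95% CIs, which fits the mean (SD) summary already planned.

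Keep Kruskal-Wallis for non-normal variables, and state that a significant result shows a difference in distributions, not in means or medians alone. No log transformation is needed for this correction.

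The cost is about two sentences of wording and a negligible loss of power when variances are equal. Estimates and standard errors from the robust linear model also pool directly over the planned multiple imputations. The article reports no comparative results, so the rule can be settled before the syndrome groups are compared.

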## Results

This trial was registered on November 17, 2024. Participant recruitment for this study was initiated in November 2024. As of October 2025, more than 450 eligible participants have been enrolled and have completed data collection. Recruitment is scheduled to conclude on December 31, 2025.

## Discussion

### Overview

DM poses a critical global health challenge, with 65%-85% of individuals with T2DM also meeting the diagnostic criteria for MetS [5,6], underscoring a widespread profile of metabolic dysregulation. Given the high comorbidity, this large-scale cross-sectional study will be the first in Hong Kong to systematically characterize the distribution of TCM syndromes in this population. It will explore how TCM syndromes relate to important health-related behaviors such as physical activity, diet, and sleep quality, as well as quality of life. By clarifying the relationship between TCM syndromes and metabolic profiles, this study aims to combine TCM assessments with clinical indicators, support more tailored treatments, and underscore the value of TCM syndrome differentiation in managing and predicting outcomes in patients with T2DM and MetS.

### Anticipated Principal Findings

Although TCM syndrome distributions in patients with T2DM and MetS have been previously examined separately [16,33,34], this study specifically focuses on their comorbidity. We anticipate that the TCM syndrome profile of T2DM-MetS comorbidity will demonstrate a distinct distribution pattern compared to either condition alone, exhibiting unique relationships with disease duration and severity. Given that both conditions represent independent cardiovascular risk factors, we further hypothesize that specific TCM syndrome patterns will correlate with particular metabolic abnormalities and varying risks of disease progression. Through the combined application of FSRS and retinal imaging, we will be able to quantitatively characterize cardiovascular risks across different syndrome patterns. Furthermore, we expect these TCM syndromes to be influenced by modifiable health behaviors and associated with differences in the quality of life. Collectively, these findings will provide evidence supporting the clinical value of TCM syndrome differentiation in prognostic stratification and personalized management of T2DM and MetS.

### Strengths and Limitations

This study has several strengths, including its design as the first large-scale cross-sectional investigation systematically characterizing TCM syndromes in individuals with T2DM and MetS. This research innovatively integrates clinical indicators such as biochemical profiling and retinal imaging with TCM syndrome differentiation while also incorporating evaluations of health behaviors and quality of life. However, several limitations should be acknowledged. The cross-sectional design inherently prevents establishing causal relationships, and reliance on self-reported data may introduce recall bias. Additionally, potential confounding factors could affect result interpretation, and the generalizability of the findings beyond the studied population requires further validation.

### Implications for Practice or Research

The findings may provide practitioners with a practical framework for incorporating TCM syndrome differentiation into T2DM and MetS management. By identifying syndrome patterns associated with metabolic profiles and lifestyle factors, this approach supports personalized treatment strategies that combine biomedical and traditional diagnostic perspectives. The integration of retinal imaging and cardiovascular risk assessments with TCM diagnostics further provides a model for comprehensive evaluation in integrative medicine practice.

Beyond these clinical implications, this study underscores the need for validated TCM syndrome assessment tools to standardize future research. It also calls for longitudinal research to establish causal relationships between syndrome patterns and disease progression. Further investigation is warranted to explore the biological mechanisms underlying identified syndrome configurations, potentially through multi-omics approaches [35]. Intervention trials targeting specific syndrome patterns would advance evidence for personalized TCM therapies.

### Conclusion

This study will first systematically characterize TCM syndromes in patients with T2DM and MetS by integrating clinical indicators with traditional diagnostic approaches. The findings are expected to reveal significant relationships between syndrome differentiation, metabolic parameters, lifestyle factors, and disease progression. This work may establish a framework for incorporating TCM syndrome differentiation into chronic disease management, thereby contributing to the development of personalized treatment strategies and improved patient outcomes in integrative medicine practice.

### Dissemination

Results will be disseminated through peer-reviewed journals and presentations at international conferences focused on metabolic disorders, ensuring accessibility to clinicians, researchers, and policymakers.

## Data Availability

The datasets generated or analyzed for this study are available from the corresponding author on reasonable request.

## Appendix

Multimedia Appendix 1 STROBE checklist.

## Abbreviations

DM: diabetes mellitus
FSRS: Framingham Stroke Risk Score
MetS: metabolic syndrome
REDCap: Research Electronic Data Capture
SDQTM: Syndrome Differentiation Questionnaire for Type 2 Diabetes Mellitus and Metabolic Syndrome
STROBE: Strengthening the Reporting of Observational Studies in Epidemiology
T2DM: type 2 diabetes mellitus
TCM: Traditional Chinese Medicine
